#### Secondary endpoints

Secondary endpoints include pain flare at 24–48-72 h after radiotherapy, the duration of pain response, re-irradiation need, toxicity, HRQoL and subsequent SSE. Pain flare at 24–48-72 h after radiotherapy is defined as pain progression according to the consensus statement [9]. Duration of pain response starts at response until pain progression. Toxicity will be measured with the Common Terminology Criteria for Adverse Events (CTCAE) version 5.0 at 1 month after RT and three-monthly during the first year after treatment. HRQoL is measured by the EORTC QLQ-C30 general questionnaire and the bone metastasis-specific module, the EORTC QLQ-BM22 [10]. Patients fill out these questionnaires before the start of RT (baseline), 1 month after RT (primary endpoint) and three-monthly during the first year after treatment (follow-up). Subsequent SSE is defined as symptomatic pathologic fractures, radiation or surgery to bone, and spinal cord compression.

### Eligibility criteria

Eligible patients are patients with a pain score ≥ 2 on a scale from 0 to 10 (measured as the worst pain for the previous 3 days at the index site), with radiological or (bone) scintigraphic evidence of bone metastasis at the site of pain and no more than 3 painful lesions needing treatment. If analgic dosing adjustment is done less than 1 week before initiation of irradiation, a run-in period is recommended to minimize the risk that the analgesic effects will confound the measurement of the RT effects. Patients should have a life expectancy estimated at > 3 months. Per lesion, no more than 3 consecutive spine segments should be involved, with one unaffected vertebral body above and below. Bone metastasis in previously irradiated sites, or originating from myeloma, or complicated bone metastasis, i.e. impending and/or existing pathological fracture, spinal cord compression or cauda equina compression [11], should be excluded.

### Trial treatments

For patients in the standard arm, the current standard treatment will be prescribed, i.e. a single fraction dose of 8.0 Gy to the metastasis with a planning target volume (PTV) margin for set-up and positioning uncertainties of 1 cm. This can be performed at any linear accelerator.

In the experimental arm, treatment will be delivered within the framework of SBRT. A single fraction dose of 20.0 Gy will be delivered to the metastasis using a PTV margin of 3–5 mm based on high-precision IGRT. Therefore, only linear accelerators with the European Organization for Radiotherapy & Oncology advisory committee on radiation oncology practice (ESTRO-ACROP) specifications for SBRT can be accepted [12]. A risk-adapted approach will be applied, aiming for the highest possible dose no less than 16 Gy, while respecting the tolerances of critical organs at risk (e.g. spinal cord, cauda equina, brainstem etc.).

### Radiotherapy details

#### Simulation and immobilization

Patient immobilization and CT simulation will be done similarly as described in a previous published study protocol from our research group on SBRT for bone metastases [13].

#### Target contouring

The gross tumor volume (GTV) will be delineated as visualized on CT. No clinical target volume (CTV) will be delineated in the experimental arm. In the standard arm standard CTV margins (e.g. incorporating the entire vertebra) are allowed. A planning target volume (PTV) will be created, allowing for daily set-up variance and organ motion. In the standard arm, PTV margins of 1 cm are common, in the experimental (SBRT) arm, PTV margins are 3 to 5 mm.

#### Organs at risk

The organs at risk (OARs) depend on the localization of the metastases. At least all OARs for which dose constraints are described in the report of the American Association of Physicists in Medicine (AAPM) task group 101 [14], lying within the scanned range on the planning CT scan, should be delineated. For spinal lesions, MRI is recommended for spinal cord delineation. A Planning Organ at Risk Volume (PRV) expansion of 2-5 mm will be added to the spinal cord, oesophagus, mediastinum, liver, heart and kidney for setup uncertainty or organ motion. If no MRI is used for delineating the spinal cord, the whole spinal canal should be delineated as PRV. All dose constraints apply to this PRV and should not be exceeded. In case of an overlap of the target with an OAR or PRV, target coverage can be lowered in order to meet the constraint.

#### Treatment planning

In the standard arm, 3D-conformal radiotherapy with basic image-guidance will be used. In the experimental arm, static or rotational treatment planning will be applied depending the localization of the metastasis. Three-dimensional or intensity-modulated coplanar or non-coplanar beam arrangements will be custom designed for each case to deliver highly conformal dose distributions. For high dose-hypofractionated radiotherapy, typically, ≥ 10 beams of radiation are used with roughly equal weighting. When static beams are used, a minimum of 7 beams should be used and non-opposing, non-coplanar beams are preferable. For arc rotation techniques, a minimum of 340 degrees (cumulative for all beams) is warranted.

#### Dose prescription and constraints

In the standard setting, 95% of the PTV should receive 95% of the prescribed dose while near maximum dose (Dnear-max) in the PTV should not exceed 107%. In the experimental arm, treatment will be prescribed to the periphery of the target, i.e. 80% of the dose should cover 95% of the PTV. In the experimental arm, coverage of PTV with the prescribed dose (20Gy) should be optimized to reach 90% or more. Coverage of the PTV with 80% of the prescribed dose (16Gy) should at least reach a minimum of 80% of the PTV with no violations of treatment planning objectives for OAR. Coverage of < 90% of the PTV with 16Gy is a Variation Acceptable, and any coverage of < 80% of the PTV with 16Gy is Deviation Unacceptable. The OAR dose constraints will be in accordance with the recommendations from the report of the AAPM task group 101 [14]. Maximum PTV dose up to 140% is allowed but all dose > 105% should be contained within the GTV. A dose fall-off outside the PTV extending into normal tissue structures should aim at 50% of the prescribed dose within 3 cm.

#### Delivery and verification

In the standard arm, image-guidance will consist of portal images showing the relevant bony anatomy. For the experimental arm, treatment will be delivered with 6–18 MV photons of a linear accelerator with ESTRO-ACROP specifications for SBRT [12]. Image-guidance will consist of cone-beam CT in combination with 6 degrees of freedom corrections using robotic couch. No other RT than photon therapy is permitted. The same position and immobilization/support device(s) as used in the planning CT scan should be utilized. For the investigational arm, a pre-treatment patient-specific and treatment verification quality assurance (QA) program based on transmission dose measurements and cone-beam CT data will be performed.

#### Treatment compliance

Radiotherapy dosing and delivery will be assessed by coverage and dose on target volumes GTV, CTV (if used) and PTV and must be captured in the source documents and the eCRF.

### Interventions

The screening procedures will determine subject eligibility according to inclusion and exclusion criteria. The following evaluation/assessments will be performed at the screening visit within 20 days of Day 1 (Table 2):
Obtain informed consentRecord the numeric pain rating scaleRecord the daily oral morphine equivalent (OMED) and other analgesicsRecord education level and computer experienceCollect details of disease and concurrent systemic anticancer treatmentECOG performance statusHRQoL questionnaires (and reason for non-compliance, if applicable)Toxicity (using the most recent version of CTCAE)

**Table 2 Tab2:** Trial flowchart

	Screening	Treatment					Follow-up
		Simulation	During study				Year 1
			RT	24–48-72 h	weekly	1 m	Every 3 m
Informed consent	x						
Registration of education level, computer experience^a^	x						
Randomization: 1 × 8.0 Gy 1 × 20.0 Gy		x					
Numeric Pain Rating Scale	x		x	x	x	x	x
ECOG performance status	x		x			x	
OMED + other analgesics	x		x	x	x	x	x
Registration of toxicity						x	x
Registration of QoL^b^	x					x	x
Registration of treatment data^c^			x				

^a^Education level:highest level of education (none, primary school, secundary school or higher education); computer experience: at least once a week access to computer/e-mail (yes or no)

^b^QoL according to the EORTC QLQ-C30 & BM22 questionnaires; if form is not completed, reason for non-compliance will be documented in compliance form

^c^See Section “Treatment compliance”

At Day 1, randomization and computed tomography (CT) simulation will be performed.

The following assessments must occur on the day of radiotherapy treatment (Table 2):
Record the numeric pain rating scaleRecord the daily oral morphine equivalent (OMED) and other analgesicsCollect RT dosing and delivery detailsECOG performance statusHRQoL questionnaires (and reason for non-compliance, if applicable)Toxicity (using the most recent version of CTCAE)

At 24 h, 48 h, 72 h, 1 week (+/− 3 days), 2 weeks (+/− 3 days) and 3 weeks (+/− 3 days) after RT subjects are asked to rate their pain flare and record concurrent medications in a pain diary.

The following procedures are to be conducted at primary endpoint visit (1 month after RT) and at each follow-up visit every 3 months up to 12 months (Table 2):
Record the numeric pain rating scaleRecord the daily oral morphine equivalent (OMED) and other analgesicsRecord the need for re-irradiationRecord the presence of a symptomatic skeletal eventDetermine the pain responseECOG performance statusHRQoL questionnaires (and reason for non-compliance, if applicable)Toxicity (using the most recent version of CTCAE)

### Statistical analysis

#### Sample size calculation

Currently, a complete pain response rate of maximum 25% after a single fraction of 8.0 Gy can be assumed [1–3]. With 116 patients, we can show a statistically significant increase to 50% in complete pain response (with Type I error of 0.05 and power of 0.8). Assuming a drop-out rate of 10%, we need to include 126 patients.

#### Data analysis

All data will be prospectively collected. Electronic case report forms will be used. Statistics will be carried out using the latest version of R.

### Safety

Suspected unexpected serious adverse reactions (SUSARs) that result in death or are life threatening will be reported to the minister and the competent ethics committee within 7 days. All other SUSARs will be reported within 15 days following notification. Once a year throughout the experiment, an annual safety report shall be provided to the ethics committee, listing all suspected serious adverse reactions which have occurred over this period, as well as a report on the safety of the participants. Regarding those adverse events and serious adverse reactions the Principal Investigator will take all reasonable measures to protect subjects at risk following the occurrence of such events. Compensation for any damages incurred by a study patient and linked directly or indirectly to the participation to the study is provided through insurance.

### Supplementary analysis

It is well established that patient and clinician symptom reports are discrepant, with clinicians generally underreporting the incidence and magnitude of symptoms compared with patients [15]. Patient-reported outcome questionnaires assess topics a patient can report about his or her own health, including symptoms, physical functioning, and mental health. Patients report this information via questionnaires that have been rigorously developed. Patient-reported outcome measures (PROM’s) assessed in cancer randomised controlled trials provide valuable information on the impact of treatment from the patient’s perspective. There is even evidence that using PROM’s in palliative oncological patients improves overall survival [16].

Yet, shortcomings in PROM’s trial design, methodology and reporting may limit the interpretation of these data. When patient responses are utilized as measures of primary and secondary endpoints, completion of required assessments is necessary to draw proper conclusions [17]. Efforts should be made to ensure patient-compliance, in order to provide complete datasets. Non-compliance with planned questionnaires and missing data can threaten both internal validity and generalizability. Administrative failure is one of the most important factors leading to non-compliance, against others like patients age [18].

Using electronic PROM’s has some important advantages over using paper-and-pencil questionnaires, e.g. reducing missing data within one assessment, implementing complex skip patterns, eliminating ambiguous data, reducing effort and error in entering data, registering response time, and real-time monitoring of PRO, to name a few. A study evaluating the impact of collecting PROM’s electronically showed greater benefits for computer-inexperienced patients, who were overall older, frailer, and more symptomatic than computer-experienced patients [16]. Participants lacking computer experience may have less-developed health communication skills and thereby benefit more from a structured program for eliciting symptoms. A negative effect of collecting PROM’s electronically is that this reduces physical communication and interaction between the patient and the medical staff.

As a supplementary analysis, we will compare patient-compliance for a paper-and-pencil with an electronic mode. Multiple studies support the between-mode equivalence of paper-and-pencil and electronic PROM’s [19, 20]. For the first 63 patients, a booklet with questionnaires (pain diary, QLQ-C30, BM22) will be presented at the visits as defined per protocol. For the last 63 patients, a smartphone app will be installed on the patient’s own smart device, in order to complete the same questionnaires electronically. During each visit, the reason for non-compliance will be documented when a patient does not complete any part of a questionnaire as required per protocol.

Logistic regression techniques will be employed to determine if any patient characteristic (e.g. socio-economic status, educational level, migration background) or clinical events influenced patient compliance.

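### Paper goes to the first 63 patients and the app to the last 63, so the compliance comparison cannot separate mode from calendar period, and device ownership adds a bias of unknown direction

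*Protocol article*

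**What the plan says.** The Supplementary analysis section states the aim: "we will compare patient-compliance for a paper-and-pencil with an electronic mode". It then fixes who receives which mode: "For the first 63 patients, a booklet with questionnaires (pain diary, QLQ-C30, BM22) will be presented at the visits", and "For the last 63 patients, a smartphone app will be installed on" a smart device that the patient owns. The reason for any non-completion is to be documented at each visit. A logistic regression will look for patient characteristics, with "socio-economic status, educational level, migration background" as examples, and clinical events that influence compliance.

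Three other parts of the article bear on this:

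- Study design randomises the radiotherapy arm only, 1:1, in blocks of four, with an electronic tool.
- Eligibility criteria do not require a smart device.
- The screening list and Table 2 include "Registration of education level, computer experience". A footnote defines computer experience as weekly access to a computer or e-mail. Ownership of a smart device is not listed.

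The abstract and the section heading call the comparison supplementary. The Background calls it a secondary aim. It is not among the secondary aims in Study design or under Secondary endpoints.

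**The concern.** Mode is decided by order of entry, so no stretch of recruitment contains both modes. Whatever changes between the two halves of the trial (site staff learning the procedures, centres opening, case mix) will be read as an effect of the app. The article makes such drift plausible: it names administrative failure as one of the main causes of non-compliance, and sites may improve on that with experience.

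The second problem is who can use the app. The paper cohort takes every patient, but in the second half only owners of a device can use the electronic mode. The same section cites a study of electronic collection that singled out "computer-inexperienced patients, who were overall older, frailer, and more symptomatic than computer-experienced patients". Digital access may therefore go with features that also affect questionnaire completion.

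At stake is whether the trial can say anything about mode. If the rule is followed exactly, a difference between the cohorts has no clear interpretation.

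**Working it through.** **1. Inputs.** From the article: 63 paper + 63 app = 126, the whole planned sample. It gives no compliance rate, target difference, power or ownership rate for this comparison. Every rate below is an assumption, shown over a range.

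**2. How far mode and time can be separated.** Number the patients i = 1 to 126 and set m = 1 if i > 63, otherwise 0. The correlation of m with i is 0.866, so R² = 0.750 and the variance inflation is 1/(1 − 0.750) = 4.0. Adjusting for a straight-line trend therefore doubles the standard error of the mode effect. With 70% compliance in both cohorts, the unadjusted standard error is √(2 × 0.70 × 0.30/63) = 8.2 points, which becomes about 16 points. Even this relies on the trend being linear. A step change at patient 64 is the same variable as m, and no model can separate the two.

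**3. What drift alone would do.** Assume 70% on paper, no mode effect and a drift of d between the halves. For a two-sided 5% test, the chance of a significant result is about Φ[(d − 1.96·SE₀)/SE₁], where SE₀ is the pooled and SE₁ the unpooled standard error. For d = 0.10:

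- SE₀ = √(2 × 0.75 × 0.25/63) = 0.0772
- SE₁ = √((0.70 × 0.30 + 0.80 × 0.20)/63) = 0.0766
- (0.10 − 0.1512)/0.0766 = −0.67, which gives 25%

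| Drift (points) | Chance of a significant result (nominal 5%) |
|---|---|
| 5 | 9% |
| 10 | 25% |
| 15 | 52% |
| 20 | 81% |

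**4. What ownership alone would do.** Let w be the share of owners, c₁ the compliance of owners and c₀ that of non-owners, with no mode effect and no drift. The paper cohort shows w·c₁ + (1 − w)·c₀.

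- Non-owners left out of the app cohort: it shows c₁, so the difference (app minus paper) is (1 − w)(c₁ − c₀).
- Non-owners kept and counted as non-completers: it shows w·c₁, so the difference is −(1 − w)·c₀.

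| Ownership w | Left out (c₁ = 0.75, c₀ = 0.50) | Counted as non-completers (same rates) | Counted as non-completers (c₁ = c₀ = 0.70) |
|---|---|---|---|
| 90% | +2.5 | −5 | −7 |
| 80% | +5 | −10 | −14 |
| 70% | +7.5 | −15 | −21 |
| 60% | +10 | −20 | −28 |

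The sign depends on a counting rule that the article does not state.

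**5. The treatment comparison.** Mode depends on entry order and not on arm. With a single list in blocks of four, the first 63 patients are 15 full blocks (60 patients) plus three from the next block, which must split 2:1. That gives 32 against 31. If the blocks run by centre, which the article does not say, each open block could add an imbalance of at most two.

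**The case against.** The strongest case on the other side is that this is a labelling matter. The analysis is supplementary in the abstract and in its own section, and no test, power or causal claim is attached to it. The ownership bias is small in mild scenarios: with owners at 80%, non-owners at 60% and 35% without a device, leaving non-owners out gives 0.35 × 0.20 = 7 points. The standard error at 80% against 73% is √((0.80 × 0.20 + 0.73 × 0.27)/63) = 7.5 points. A rule for patients without a device may stand in the full protocol, which an article need not repeat. Parallel running of two systems is also more work than one extra screening item.

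Much of this stands. It limits the importance of the point, and a fallback for non-owners could change the ownership part. It does not touch the calendar part, because the allocation by entry order is stated outright and any fallback leaves it in place. A bias below one standard error is still a bias, and it adds to any drift.

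A reader might infer four stronger things that the article does not support:

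- **That selection must favour the app.** This assumes that non-owners are dropped, which the article does not say. The sentence on computer-inexperienced patients also reports greater benefit from electronic collection in them, and weekly computer access is not device ownership.
- **That age is the main driver of non-compliance.** The article puts administrative failure first and mentions age among other factors.
- **That the regression omits computer experience, or relies on variables nobody collects.** The covariates are given only as examples, and a condensed flowchart does not show everything on the case report form. The regression's stated purpose is to find predictors of compliance, not to adjust the mode contrast.
- **That the switch undermines the treatment result because the pain diary changes mode too.** At any point in recruitment both arms use the same mode.

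**Conclusion.** The point holds for the supplementary comparison. Mode is fully confounded with calendar period by a stated rule, and no later analysis can fully repair that. Under an assumed 70% compliance on paper, a drift of 10 to 15 points would produce a significant difference in roughly a quarter to a half of trials with no mode effect. Device ownership is a second source of bias of unknown sign: from +2.5 to +10 points if non-owners are left out, and from −5 to −28 points if they count as non-completers, over assumed ownership of 90% to 60%. These sizes are illustrations; the confounding itself does not depend on them. The randomised comparison of the two radiotherapy arms is not affected. The change is worth making because the design flaw is certain and the remedy is inexpensive, but the trial's main conclusions do not depend on it.

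**What to change.** **If the mode phases can still be changed.** Record smart-device ownership at screening for every patient. Among owners, allocate paper or app 1:1 at random with the existing electronic tool, stratified by treatment arm. Non-owners use paper and are reported separately. Analyse by assigned mode, with computer experience and education, both already collected, as covariates. Because the arm is drawn on Day 1, after the screening questionnaires, mode would be drawn at the same moment and the screening questionnaires would stay outside the comparison.

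**Cost.** One screening item and a second allocation in the tool. Paper and app must run in parallel at all centres. The randomised comparison covers owners only: at an assumed 60% to 90% ownership, 0.60 × 126 ≈ 76 to 0.90 × 126 ≈ 113 patients instead of 126.

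**If the paper phase has already run.** Record ownership from now on, and retrospectively where possible. Keep all patients in their assigned cohort in the main analysis, and report compliance with and without non-owners. Label the result a non-randomised before-after comparison that cannot separate mode from period. Adjusting for entry date should not be offered as a cure, and restricting to owners is possible only where ownership in the paper cohort can be recovered.

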## Discussion

In this report, we present the rationale and design of the ROBOMET trial, a randomized study in radiotherapy for painful bone metastases investigating whether SBRT can increase the pain response while at the same time limit the side-effects. It is clear that, although palliative antalgic radiotherapy is an established treatment for painful bone metastases, there is important room for improvement, both regarding efficacy as well as toxicity. Many costly bone-targeted therapies such as osteoclast inhibitors as well as radiopharmaceutical agents have been developed, but palliative radiotherapy remains the mainstay for local treatment and symptom control. It is therefore to be expected that this patient-directed trial can improve the quality of life of a great number of cancer patients worldwide on short term.

One important measure to improve pain response to radiotherapy would be to escalate the dose delivered to the tumor. Evidence for this emerges from multiple prospective studies. Researchers from Ghent University Hospital randomized (1,1:1) 45 patients with uncomplicated painful bone metastases to receive either 8.0 Gy in a single fraction with conventional radiotherapy (arm A) or 8.0 Gy in a single fraction with dose-painting by numbers IMRT up to 10.0 Gy (arm B) or 16.0 Gy in a single fraction with dose-painting by numbers IMRT up to 18.0 Gy (arm C). The primary endpoint was overall pain response at 1 month. Eight (53%), 12 (80%) and 9 patients (60%) had an overall response to treatment in arm A, B and C, respectively [21]. In an American single-institute series, 49 patients with 61 separate spinal metastases were treated to a single fraction of 10.0 to 16.0 Gy [22]. Encouragingly, complete pain relief was achieved in 46%, partial relief in 18.9%, and stable symptoms in 16.2% of patients. These data suggest that a single dose-escalated fraction could result in complete pain response rates of around 50%.

A major advantage of SBRT over 3DCRT is an expected reduction in dose to the normal tissue, which presumably will lead to less acute toxicity. Already numerous case series and multiple prospective trials have proven that both multi- and single fraction SBRT schedules for bone metastasis can be delivered with minimal toxicity [23–27]. Especially in a palliative setting, even transient side effects like nausea and diarrhoea are cumbersome. In this regard, optimisation of palliative radiation treatment through the use of SBRT is one of the measures that should be investigated, because quality of life is for most of these patients of ultimate priority.

On the other side, some reports indicate that high dose single fraction SBRT is associated with a greater incidence of pain flare. In prospective studies using 3DCRT for painful bone metastases, the incidence of pain flare is approximately 40% [28, 29] whereas this incidence ranges between 10 and 68% after SBRT [30–34]. One explanation for this large range is the difference in fractionation schedules that are used, with a single fraction SBRT potentially leading to more pain flare. Besides that, inconsistency in the definitions of pain flare, the use of retrospective data, administering corticosteroids in the prevention of pain flare, or physicians rather than patients reporting pain scores, are other factors making it difficult to compare between these results.

A potential disadvantage of SBRT could be the higher rate of vertebral compression fractures (VCF) associated with this technique. At least in the spine, the use of high dose single fraction SBRT might be associated with a higher risk of vertebral compression fractures. In a large multi-institutional investigation of spine SBRT related VCF, a dose-complication relationship was observed based on the dose-per-fraction. A 39% risk of VCF was observed with high dose single fraction SBRT (≥24 Gy), 23% with a dose per fraction of 20 to 23 Gy, and 11% when below 20 Gy [35]. In order to identify patients who are stable, potentially unstable or frankly mechanically unstable, the Spinal Instability Neoplastic Score (SINS) was developed [36], which incorporates several of the significant predictive factors on either uni- or multivariate analysis of trials evaluating VCF after SBRT [37]. Most VCF are observed shortly after SBRT, with a median time to VCF of 2.6 months according to the systematic review of Faruqi e.a [37]. However, in the calculation of this median time to VCF, a study with a median of 25 months was treated as outlier and excluded [38]. In order to evaluate the incidence of VCF in our patient cohort, serious SSE will be evaluated until 1 year after completion of treatment, which we believe will capture most of the treatment-related VCF’s.

To our knowledge, there are no published randomized trials comparing conventional to stereotactic radiotherapy in polymetastatic cancer patients with bone metastases, but multiple other trials have been initiated to look at the efficacy and safety of SBRT for painful (spinal) bone metastases. The American RTOG-0631 trial aimed to randomize (1:2) 240 patients with localized spinal metastases between a single conventional RT fraction of 8.0 Gy vs. a single SBRT fraction of 16.0 or 18.0 Gy (with dose as preferred by the treating physician). Primary endpoint is complete or partial pain relief at the treated index site at 3 months. Accrual has recently finished and results are awaited [39]. This trial is clearly very similar but focussed exclusively on spinal metastases, where the dose is limited due to the proximity of the spinal cord. Another trial is the Dutch VERTICAL trial, aiming to randomize (1:1) 110 patients with painful bone metastases to either between a single conventional RT fraction of 8.0 Gy vs. a single MRI-based SBRT fraction of 18.0 Gy to the visible metastasis and 8.0 Gy to the bony compartment containing the metastasis. Primary endpoint is complete or partial pain response at 3 months after radiotherapy. This trial is currently still recruiting [40]. Recently, the results of a randomized trial of the Heidelberg University were published. In this trial, 55 patients with painful spinal metastases were treated with either single fraction SBRT (24Gy) or 3DCRT (30Gy in 10 fractions). The trial demonstrated that single-fraction SBRT reduced pain levels faster during the 3 months following RT and led to improved pain scores compared to 3DCRT.

Currently, the innovations (IMRT, IGRT) that have fuelled many of the significant advances in curative radiotherapy are not sufficiently being applied for palliative indications. This is partly due to limited resources, since these new techniques take up more time on the treatment machine and also more extensively occupy health care providers, both physician, physicist and radiation therapist, compared to conventional radiotherapy. However, by minimizing subsequent re-irradiation, reducing pain medication and preventing costly SSEs, this new technique can have a favourable socio-economic impact. Therefore, randomized evidence supporting the utility of advanced technologies in the palliative setting will be needed to convince both the radiation oncology community as well as the relevant governments and reimbursement agencies of the need to apply these innovative techniques to palliative patients.

